### Baseline assessment

Sociodemographic characteristics will be acquired via the Canadian minimum dataset self-reported questionnaire at baseline, after randomisation.^65^

### Outcome measures

#### Primary outcome

##### Disability

##### Disability

The Oswestry Disability Index (ODI) will be used to measure participants’ level of self-reported disability in relation to LBP and common daily activities. This is a 10-item scale, which also includes pain severity outcomes, where each item is rated from 0 to 5 and higher scores are indicative of greater disability. This scale is the most commonly used to assess disability in LBP populations and has evidence of validity, reliability and responsiveness.^66^

### Secondary outcomes

#### Multifidus muscle composition

All participants will undergo a lumbosacral MRI evaluation using the School of Health’s (Concordia University) 3.0 Tesla GE scanner (Milwaukee, Wisconsin, USA). Body position will be standardised (eg, prone with knees flexed at 30°). Sagittal and axial T2-weighted (repetition time (TR): 3800, echo time (TE): 98) and axial 3D spoiled gradient-echo images using a 2-point Dixon fat-water separation technique (Lava-Flex, dual-echo acquisition; TE: 4.5, TE: minimum full, flip angle: 5) of the entire lumbar spine will be obtained for a total acquisition time of about 7 min. A standard phased-array body coil with 16 channels will be used, with 4 mm slice thickness, 180 mm^2^ field of view and 512×512 matrix. MRI slices will be acquired in a single block, and slice orientation will be standardized post-acquisition;^27^ coregistration will be used between time points. Multifidus muscle composition (eg, intramuscular fatty infiltration) will be assessed bilaterally at each lumbar level using the fat and water images, by calculating percent-fat signal fraction (%FSF) at each level using the following equation: %FSF=(Signalfat/[Signal water+SignalFat]×100). The %FSF will be measured automatically using convolutional neural networks (CNNs) with excellent reliability and validity, extensively studied by our research team.^67 68^

#### Multifidus muscle size

Multifidus cross-sectional area and cumulative 3D volume from MRI slices at each lumbar level (bilaterally) will be measured automatically using CNNs with excellent reliability and validity, extensively studied by our research team.^67 68^

#### Lumbar extensor muscle strength

Lumbar extensor muscle strength will be assessed with the use of the MedX Lumbar Extension Machine. The pelvis restraint system will be used to ensure isolation of the lumbar extensor muscles with the axis of movement being fixed between the vertebral levels of L5-S1. This dynamometry assesses isometric lumbar extension muscular strength (torque) in a seated position and accommodates the dynamic resistance through a full 72° ROM. Thus, maximum lumbar isometric contraction (Maximum voluntary isometric contraction, MVIC) in lumbar extensor muscle strength will be assessed in seven positions: 72°, 60°, 48°, 36°, 24°, 12° and 0° of flexion.^53 60 69^ Participants will first perform a controlled warm-up for approximately 1 min, and maximum strength testing will then begin.^69^ Verbal encouragements will be provided to encourage participants to generate maximum torque. The movement arm of the MedX machine is attached to a load cell that is interfaced with a computer recording the torque measurements.

#### Gluteal muscle strength

A handheld dynamometer VALD DynaMo (VALD Performance, Brisbane, Queensland, Australia) will be used to assess gluteal muscle strength. Participants will be placed on a therapy table in a prone position with their arms by their side to assess the gluteus maximus muscle strength with the knee at 90 degrees of flexion and the thigh/hip slightly extended (eg, off the table). Participants will be instructed to maintain this position for 5 s, creating an isometric contraction in the form of a ‘make’ test and asked to exert a maximal force against the handheld dynamometer. Measurements will be recorded in newton/torque. All participants will have a submaximal practice trial and then three measurements will be obtained on each side, with a break of 30–45 s in between each trial. The mean of the three measurements will be used in the analysis. Similarly, patients will be placed in a side-lying position with their arms by their side and with their top leg abducted, slightly extended and externally rotated to test the gluteus medius muscle. Again, participants will be instructed to maintain this position for 5 s, while exerting a maximal force against the handheld dynamometer. Three measurements will be acquired on each side. Handheld dynamometry has been shown to be a valid^70^ and highly reliable tool to assess gluteus muscle strength^71^ and has been recommended as a practical standard for clinical settings.

#### Hip ROM

Hip ROM and flexibility in flexion and extension will be assessed using the VALD DynaMo handheld dynamometer (VALD Performance), following standardised testing procedures. Each movement will be measured three times, and the average will be calculated. To minimise compensatory movements and ensure consistency, the hip will be stabilised using the ROM strap. For hip flexion, the participant will lie supine with both knees flexed at 90 degrees and will be asked to bring their knees to their chest. The VALD DynaMo will be attached to the lateral aspect and distal end of the test thigh. For hip extension, the participant will lie prone with both legs straight and will be instructed to lift their heels to the ceiling; the device will be fixated to the lateral side and distal thigh using the ROM strap. A handheld dynamometer VALD DynaMo will also be used to assess hip flexibility (flexion, extension). Hip flexibility will also be assessed using the DynaMo Plus. The straight leg raise test will evaluate hamstring flexibility, with the participant lying supine and the evaluator lifting the leg as high as possible while the device is attached to the distal lateral thigh. The modified Thomas test will assess hip flexor flexibility, with the participant seated at the edge of the table, grasping one knee to the chest and slowly lying supine on the table, while the opposite leg hangs freely over the edge of the table with the device attached to the lateral distal thigh using the ROM strap. The VALD DynaMo Plus has demonstrated excellent reliability for strength and ROM assessment, with intraclass correlation coefficients exceeding 0.90 in most tests.^72^

#### Impact of LBP: Patient-Reported Outcomes Measurement Information System

The Patient-Reported Outcomes Measurement Information System (PROMIS-29) v2.0 evaluates seven domains with four questions each, including: physical function, anxiety, depression, fatigue, sleep disturbance, ability to participate in social roles and activities, and pain interference and intensity.^73^ This questionnaire will be used to assess pain and how it interferes with physical and mental function.

#### Pain

We will monitor pain level with the Numerical Rating Scale (NPR) from 0 to 10 (where 0 is no pain and 10 is the most extreme pain) using the ‘*Manage My Pain’* app to assess weekly pain level. Both PROMIS-29 and NPR have excellent reliability and validity and can be used to detect clinically significant changes in perceived pain.^74 75^

#### Health-related quality of life

The 12-item Short Form Health Survey is the condensed form of the previous 36-item survey and will be used to assess participants’ health-related quality of life. The 12-item survey consists of eight domains that assess both physical and mental components of health. Scores from each of the 12 questions are combined to give an overall score between 0 and 100, with a score of 100 indicating the highest level of health. Given that this is a condensed version of a longer and established questionnaire, it has been extensively tested and shown to be both reliable and valid.^76^

#### Sleep quality

At both preintervention and postintervention, participants will be sent a wrist-worn actigraph (AX3, Axivity) in order to further evaluate sleep disturbance. Participants will be asked to use the actigraph for 7 days at home at both preintervention and postintervention for objective estimation of average sleep latency, wake after sleep onset, total sleep time and sleep efficiency, and will be asked to complete a sleep diary during the same period. While sleep disturbances are common in LBP, the effect of exercise on sleep quality remains to be established in this population.^77 78^

#### Level of physical activity

The International Physical Activity Questionnaire (IPAQ) will be used to measure participants’ level of physical activity. The IPAQ is a self-reported log of physical activity (metabolic equivalents (METs) based on intensity) in minutes per week over a period of 7 days. The level of physical activity is ranked either vigorous (8 METs), moderate (4 METs), walking (3.3 METs) and sitting/rest (1 MET) and must be allocated to the right category. The number of minutes per category is then combined, and the results are then organised as high, moderate or low physical activity based on the total MET minutes. The reliability and validity of this measure have been demonstrated.^79^

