### Study interventions

Participants in each group will receive 48 sessions of approximately 1 hour over a 16-week period (three sessions per week). The treatment sessions will be individually supervised by certified athletic therapists or kinesiologists. Each participant will receive a free membership card to access the School of Health conditioning floor, where all research activities will be taking place.

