#### Adherence

Adherence to the exercise programme will be assessed through multiple methods. Therapists will maintain treatment records for each participant, which will be collected at the end of the study to evaluate attendance and engagement. Participants will also be asked to maintain a personal exercise log and will be provided with a training booklet that includes their individualised programme and wipe cards for tracking progress at the School of Health. Additionally, participants will wear an activity monitor (ActiGraph AX3) for seven consecutive days prior to the intervention and again at the 16-week follow-up to objectively measure step counts and intensity minutes, providing insight into overall physical activity levels.

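### As written, the IPAQ rule counts sitting at 1 MET in the total that ranks physical activity, so more sitting raises the activity score

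*Protocol article*

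**What the plan says.** Physical activity level is one of the outcomes compared between arms under secondary aim 2 (Objectives). The section Level of physical activity names one instrument: "The International Physical Activity Questionnaire (IPAQ) will be used to measure participants’ level of physical activity". It describes a 7-day self-report with entries "ranked either vigorous (8 METs), moderate (4 METs), walking (3.3 METs) and sitting/rest (1 MET) and must be allocated to the right category". The scoring follows: "The number of minutes per category is then combined", and then "the results are then organised as high, moderate or low physical activity based on the total MET minutes". The article gives no cut-offs for the three ranks and does not say that sitting is left out of the total.

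An activity monitor is also worn for seven days before the intervention and again at the 16-week follow-up. The Adherence section gives its purpose: "to objectively measure step counts and intensity minutes, providing insight into overall physical activity levels". The Sleep quality section uses wrist actigraphy for sleep variables only: "objective estimation of average sleep latency, wake after sleep onset, total sleep time and sleep efficiency". No section lists the step counts or intensity minutes as a measure of the physical-activity outcome.

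The abstract assigns linear mixed-effects models to the primary and secondary outcomes alike.

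**The concern.** Sitting appears as the fourth weighted category, and the next sentence combines the categories into the total that sets the rank. An analyst who follows that text would add sitting time to an activity score. A participant who reports more sitting, with activity unchanged, would then move up the scale and might cross into a higher rank.

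Sitting has the lowest weight, but it can fill many hours of a day, so its contribution can be large beside that of exercise. At stake is the between-arm comparison of physical activity, where differences in sitting, or in how it is reported, would be mixed into the score.

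Two related points make the outcome weaker than it need be. A three-level rank carries less information than the score behind it and does not suit a linear mixed model. The objective activity data already planned are placed under Adherence, with no stated role in the outcome they describe.

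**Working it through.** The plan gives no IPAQ figure (score, cut-off or sitting time), so there is nothing of its own to reproduce. The check applies its stated weights.

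**Inputs from the protocol article**
- Weights: vigorous 8, moderate 4, walking 3.3, sitting/rest 1 MET (Level of physical activity).
- Supervised exercise: three sessions a week of about 60 minutes, so 3 × 60 = 180 min/week (Study interventions).

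**Assumptions, not in the article**
- Sitting time: 2 to 10 h/day.
- Intensity of the trial sessions: 4 or 8 METs.

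**Formula.** MET-min/week = sum over categories of weight × minutes per week.

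**1. Contribution of sitting.** One hour a day gives 1 × 60 × 7 = 420 MET-min/week.

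| Sitting (h/day) | MET-min/week |
|---|---|
| 2 | 840 |
| 4 | 1680 |
| 6 | 2520 |
| 8 | 3360 |
| 10 | 4200 |

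**2. Supervised programme as a yardstick.** At 4 METs: 180 × 4 = 720. At 8 METs: 180 × 8 = 1440. Sitting equals the programme at 720/420 = 1.7 h/day or 1440/420 = 3.4 h/day.

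**3. Share of sitting in the sum of sitting and programme**
- 2 h/day: 840/(840 + 720) = 54% at 4 METs; 840/(840 + 1440) = 37% at 8 METs.
- 6 h/day: 2520/3240 = 78%; 2520/3960 = 64%.
- 10 h/day: 4200/4920 = 85%; 4200/5640 = 74%.

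**4. Can the order of two participants reverse?** Two assumed profiles:
- Active: 60 min vigorous, 120 min moderate and 150 min walking per week, sitting 4 h/day. Activity: 480 + 480 + 495 = 1455. With sitting: 1455 + 1680 = 3135.
- Inactive: 60 min walking per week, sitting 9 h/day. Activity: 198. With sitting: 198 + 3780 = 3978.

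Without sitting, the active person scores higher (1455 against 198). With sitting, the inactive person does (3978 against 3135).

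**5. If activity replaces sitting minute for minute.** The net gain per minute is the weight minus 1. It shrinks by 1/3.3 = 30% for walking, 1/4 = 25% for moderate and 1/8 = 12.5% for vigorous activity, but it stays positive in every case.

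**The case against.** The strongest reply is that the article paraphrases an established questionnaire with a cited source. It never says outright that sitting minutes enter the total, and detailed scoring usually sits in a fuller document. That stands as a caution, and the wording may simply be loose. It does not remove the point, because the article states a scoring rule rather than leaving one out, and the stated rule misscores.

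Some stronger readings are tempting but not supported:
- *Sitting swamps real activity, or the outcome no longer measures activity.* How far sitting dominates depends on hours the article does not give. Replacing sitting with any listed activity still raises the total (step 5 of the working). The order reverses only between people, or over time, when sitting differs without offsetting activity.
- *A 2 h/day shift in sitting outweighs the whole programme.* That holds at 4 METs (840 against 720) but not at 8 METs (840 against 1440).
- *The 7-day recall partly measures assignment.* The recall at 16 weeks may include trial sessions, but both arms have the same number and length of sessions, so session time is balanced between arms.
- *Adherence is measured by an unsuitable device.* Therapist treatment records already cover attendance, with participant exercise logs beside them; the monitor is an addition.
- *The monitor data go unused, or should lead.* The article ties them to overall physical activity without attaching an outcome or analysis, so non-use is an inference. Making the device the lead measure is a matter of preference: unblinded wearers can change their behaviour, and the monitor week may also include trial sessions.

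**Conclusion.** The point holds in a limited form. Read as written, the rule puts sitting at 1 MET into the ranking total, so more sitting raises the activity score by 420 MET-min/week per daily hour. At an assumed 6 to 10 h/day, sitting contributes more than the supervised programme at either assumed intensity, and the order of an active and an inactive participant can reverse.

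The conclusion rests on the literal reading of a condensed text; the size rests on the assumed sitting hours and exercise intensity. Without cut-offs, the number of participants placed in the wrong rank cannot be computed. The effect is confined to one secondary outcome. The ODI comparison and the sample size do not depend on it.

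**What to change.** 1. State that total MET-minutes are the sum of vigorous, moderate and walking only, and report sitting time separately.
2. Compare the arms on the continuous (transformed) MET-minute score, in line with the linear mixed-effects models that the abstract assigns to secondary outcomes. Keep the high, moderate and low ranks as description.
3. Name the monitor's step counts and intensity minutes, already planned before the intervention and at 16 weeks, as a supporting objective measure of physical activity rather than as adherence. State whether the week of wear can include trial sessions.

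The first two changes are wording and need no new data. The third adds some processing of accelerometer files. If the sponsor regards it as an important change to the outcomes, the article's own rule calls for an ethics amendment before it is implemented.

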#### Satisfaction and Recovery Index level

The Satisfaction and Recovery Index (SRI) will be used to evaluate participants’ experience and perceived progress following the 16-week exercise intervention. The SRI is a validated patient-reported outcome measure assessing multiple dimensions of recovery, including satisfaction, perceived progress, symptom improvement and functional status.^80^ It consists of nine items rated on a 0–10 Likert scale, where higher scores indicate greater satisfaction and recovery. An importance-weighted composite score is calculated to reflect overall health-related satisfaction.

### Data monitoring

#### Adverse events

The occurrence of adverse events such as muscle soreness and transient increase in LBP levels will be monitored by the therapists throughout the intervention period and documented using open-ended questions during routine data collection follow-ups.

#### Adherence

Adherence to the exercise programme will be assessed through multiple methods. Therapists will maintain treatment records for each participant, which will be collected at the end of the study to evaluate attendance and engagement. Participants will also be asked to maintain a personal exercise log and will be provided with a training booklet that includes their individualised programme and wipe cards for tracking progress at the School of Health. Additionally, participants will wear an activity monitor (ActiGraph AX3) for seven consecutive days prior to the intervention and again at the 16-week follow-up to objectively measure step counts and intensity minutes, providing insight into overall physical activity levels.

#### Cointerventions

Participants will be asked to report any cointerventions (eg, chiropractic care, massage therapy) during each scheduled data collection follow-up. This will allow for the identification of potential crossovers. The use of pain medication will be permitted, as withholding it would be unethical; however, this information (type and dose) will be systematically recorded for both intervention groups.

### Qualitative strand

The qualitative strand is situated in a critical realist ontoepistemology,^81^ which treats knowledge and the individuals creating it as ‘contextually situated, partial, and always provisional’.^82^ Reflexive thematic analysis (RTA), as developed by Braun and Clarke,^83^ will be used within an experiential quality framework. That is, data collection and analysis are designed to capture and describe participants’ subjective perspectives.^83^ RTA is a theoretically flexible method for developing, analysing and interpreting patterns within qualitative datasets such as interview transcripts.^83^ Potential participants will be invited to take part in a one-on-one in-depth semistructured interview^84^ before starting the intervention and after having completed it. A purposive sampling strategy will be used to include individuals with varied demographic profiles, aiming for diversity of perspectives.^85^ Given the epistemological position of the qualitative strand, an exact sample size cannot be determined a priori.^86 87^ Rather, the concurrent collection and analysis of qualitative data will inform the number of participants included and orient purposive recruitment. It is provisionally estimated that 15–20 participants will be interviewed at each time point, based on prior studies with similar settings and methodologies.^88 89^ The concepts of information power^90^ and data adequacy^91^ will be used as guiding principles to determine and justify a final sample size. Semistructured interviews will take place via Zoom, a secure end-to-end encrypted video call platform.^92^ Two interview guides will be developed for the preintervention and postintervention interviews, listing questions and prompts meant to elicit information about perceptions and experiences of LBP, exercise beliefs and the present RCT. Each guide will be piloted with three participants at both time points to adjust and refine questions before continuing recruitment.^93^ Conversations will be audio recorded and transcribed verbatim and anonymised prior to data analysis. Interview transcripts will be analysed following the six phases of RTA outlined by Braun and Clarke^83^: (1) dataset familiarisation, (2) data coding, (3) initial theme generation, (4) theme development and review, (5) theme refining, defining and naming and (6) writing up. Coding will be both inductive and deductive; that is, the analysis will be grounded in participant narratives while being informed by theories including self-determination theory,^94^ social cognitive theory^95^ and the theory of planned behaviour.^96^ The following strategies will be employed to ensure methodological rigour: audit trail and reflexive journal, peer debriefs throughout data collection and analysis, and member reflections.^97^,^99^

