**Methods and analysis:**

A total of 106 participants will be recruited through primary and secondary care and randomised (1:1) to receive either MC+ILEX or free-weight resistance training. Both groups will complete 48 exercise sessions over 16 weeks. The primary outcome will be disability at 16 weeks, measured by the Oswestry Disability Index. Secondary outcomes include multifidus muscle composition and size, lumbar and gluteal muscle strength, hip range of motion, pain, physical and mental function, satisfaction and recovery, health-related quality of life, sleep quality and physical activity levels. Linear mixed-effects models will be used to assess primary and secondary outcomes. Regression analyses will explore whether baseline LSIQ scores moderate treatment effects on multifidus composition and other outcomes. A subsample of participants will undergo semistructured interviews before and after the intervention to explore their illness perceptions, illness mindsets, perceptions of exercise therapy, as well as their experiences and satisfaction with the two exercise interventions. Reflexive thematic analysis will be used to analyse qualitative data.

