It is increasingly acknowledged that the factors influencing participants’ engagement with interventions and resulting outcomes are more nuanced, dynamic and context specific than previously thought.^37 38^ For instance, mounting evidence suggests that patients’ illness perceptions, including beliefs about causes of LBP and perceived benefits of exercise, may have important impacts on treatment adherence and outcomes.^39 40^ Prior studies have noted discrepancies between quantitative measures and patient narratives,^41^ highlighting the need to investigate the complex phenomenon of LBP rehabilitation through multiple lenses.^42 43^ Careful consideration of participants’ subjective accounts is thus instrumental in moving towards context-sensitive, patient-centred care.^44^ Qualitative methods will be used to explore participants’ perceptions and experiences related to their LBP and to the two exercise interventions in the present trial. One-on-one semistructured interviews performed before and after completing the interventions will be used to collect rich data that will help shed light on potential mechanisms of treatment efficacy, identifying intervention aspects that may facilitate or interfere with the care provided.^45 46^ This line of inquiry is particularly relevant for programmes involving high doses of exercise over an extended period of time where interpersonal, motivational and environmental dimensions are expected to have important repercussions.

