### Objectives

Our primary aim is to determine which 16-week exercise intervention, namely motor control plus isolated lumbar extension exercises (MC+ILEX, arm 1) or free-weight resistance training (arm 2), is more effective in improving disability in patients with predominant nociceptive chronic LBP. Secondary aims are to (1) assess whether changes in multifidus muscle composition mediate improvements in disability; (2) compare the effects of both interventions on multifidus size and quality, lumbar extensor and gluteal strength, hip range of motion (ROM), pain, health-related quality of life, sleep quality, physical activity level, and satisfaction and recovery; (3) explore whether baseline scores on the Lumbar Spinal Instability Questionnaire (LSIQ) and sex/gender act as moderators of treatment response at 16 weeks; and (4) explore participants’ perceptions, mindsets, experience and satisfaction of exercise therapy before and after completing the 16-week interventions.

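### The second interview is worded for completers only, so the qualitative strand will under-represent reasons for stopping the programme

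*Protocol article*

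**What the plan says.** Four parts of the protocol article bear on this.

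- **Timing.** The Qualitative strand section places the two interviews "before starting the intervention and after having completed it". The Introduction describes "One-on-one semistructured interviews performed before and after completing the interventions", and the fourth secondary aim under Objectives is to "explore participants’ perceptions, mindsets, experience and satisfaction of exercise therapy before and after completing the 16-week interventions".
- **Purpose.** The Introduction says the interviews should help in "identifying intervention aspects that may facilitate or interfere with the care provided", and finds this especially relevant to long, high-dose exercise programmes. The Abstract adds that they cover illness perceptions and mindsets "as well as their experiences and satisfaction with the two exercise interventions".
- **Who is sampled.** "A purposive sampling strategy will be used to include individuals with varied demographic profiles, aiming for diversity of perspectives". No other sampling dimension is named. Analysis runs alongside data collection and "will inform the number of participants included and orient purposive recruitment".
- **How many.** "It is provisionally estimated that 15–20 participants will be interviewed at each time point".

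The programme itself is 48 supervised sessions over 16 weeks (Study interventions).

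**The concern.** The interviews are meant to bring out what helps and what hinders in a demanding programme. A participant who gives up part-way because of burden, pain, scheduling or loss of motivation has met a hindrance strong enough to end participation. The stated timing gives that person no second interview, and the stated sampling criterion gives no reason to look for them.

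At stake is the balance of the findings for the fourth secondary aim. Themes on satisfaction and barriers that come mainly from people who finished are likely to look more favourable than the experience of everyone randomised. The article lists the qualitative strand among the trial's strengths because it should improve how the interventions are delivered. Advice on delivery is weaker if reasons for stopping are absent from it.

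**Working it through.** No formula decides this point. The interview number is a provisional judgement with nothing to recompute, so the check is to set the statements side by side.

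1. **Is the completer wording a single loose phrase?** No. The Qualitative strand section, the Introduction and the Objectives all tie the second interview to completion. The Abstract is looser and speaks only of interviews before and after the intervention. No section gives an interview point to someone who discontinues.

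2. **Does the purpose need people who stop?** In part. Identifying aspects that interfere with care can draw on completers, who can describe difficulties they overcame. Only those who stopped can say first-hand why they did.

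3. **What happens to an interviewee who stops?** The text reads as though the same people are invited to both interviews, with 15–20 expected at each time point. If one of them stops, either the second set shrinks or a completer takes the place. The account of why that person stopped is lost in both cases.

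4. **Does the sampling frame correct this?** Not by what it names. The only stated dimension is demographic. Concurrent analysis may redirect recruitment, but nothing directs it towards completion or adherence status.

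5. **What does completion mean?** It is not defined for the interviews. There are two readings:
   - *Finished the programme.* The number of second interviews available to participants who stopped is 0 of 15–20.
   - *Reached the end of the 16-week period.* The Data collection section describes the 16-week assessment as the end of the intervention, which supports this reading. Poor attenders, and people who stopped exercising but stayed in contact, would then be eligible. Even so, they would be asked only at week 16, possibly long after stopping, and the frame would still not seek them out.

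6. **Can the number affected be derived?** No. The Sample size calculation allows 15% loss to follow-up: 90 / 0.85 = 105.9, rounded up to 106, so 106 − 90 = 16 participants. That counts people without a 16-week outcome. It does not count people who stopped exercising. Someone may stop and still be assessed, or may finish and miss the assessment. The article gives no discontinuation rate, so the expected number of such interviewees cannot be calculated.

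**The case against.** The strongest reply has five parts.

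- **Completers can report barriers, and the interviews before the intervention reach people who later stop.** This stands. A reader might infer that the strand cannot show what interferes with care. The documents do not support that: the guides ask about experience of back pain, exercise beliefs and the trial, and people who finish can describe burden, pain and lapses in motivation. What is missing is narrower, namely reasons for stopping.
- **The fourth aim itself refers to the time after completing the interventions, so the design follows its own aim.** This is true of the aim's wording. The tension is with the purpose given in the Introduction, and it remains.
- **Completion may simply mean week 16.** This is a fair reading and reduces the problem. It does not remove it, because the term is undefined and those who stop are not sought.
- **The trial arms will be covered.** A reader might infer that one intervention could go largely undescribed because arm is not a sampling criterion. The documents do not support that as a defect. Neither arm is excluded, allocation is 1:1, the aim is exploratory, and ongoing analysis can steer recruitment to a thinly described arm. Chance-imbalance calculations do not help, since purposive sampling is not random selection. Naming arm is a small clarification only.
- **An article condenses the full protocol, which may hold more sampling detail.** This stands for the sampling dimensions. It has less force for the timing, which the article states three times in the same sense.

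**Conclusion.** The point holds in a limited form. As worded, the second interview belongs to people who complete the intervention, while the stated purpose includes finding what interferes with care. Followed literally, the themes will lean towards completers and will lack first-hand reasons for stopping.

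The size depends on what completion means: none of the second interviews can come from people who stopped on the strict reading, and an unquantified shortfall arises on the calendar reading. It would be wrong to take the 16 participants allowed for loss to follow-up as the number affected.

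The conclusion assumes that some participants will stop early and that their reasons differ at least partly from the difficulties completers describe. Both are plausible for three supervised sessions a week over 16 weeks, but neither is given in the article. The randomised comparison, the sample size and the primary analysis are not touched. This is a modest improvement to an exploratory strand, worth making before interviewing starts.

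**What to change.** Change the wording of the Qualitative strand section, and match the Introduction and Objectives to it:

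1. Offer the second interview to every interviewee at 16 weeks or at the time of stopping the programme, whichever comes first. This also removes the ambiguity over completion.
2. Name completion or adherence status as a purposive sampling dimension alongside demographics. Add trial arm as a minor clarification. No fixed quota or equal split is needed.
3. Add a short set of prompts for people who discontinued to the post-intervention guide. The article says both guides are still to be developed.
4. In the report, state how many second interviews came from people who stopped, so that readers can judge how far the themes reach.

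The total stays within the planned 15–20 interviews per time point. The cost is the revised text, any ethics amendment it requires, and a prompt to invite people when they stop. Some who discontinue will decline, and there will be slightly fewer completer interviews. If the full protocol already provides for this, one sentence in the article is enough.
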